## Abstract

**Background:**

The global incidence of type 1 diabetes is rising, and youths with type 1 diabetes continue to suffer poorer health than peers without diabetes. Evidence suggests youths with type 1 diabetes have physical activity (PA) levels well below the recommendations for health and have high levels of sedentary behaviour. An active lifestyle is therefore recommended to improve health. There is limited research showing effective lifestyle behaviour change in this population; therefore, an evidence gap exists between the need to promote physical activity in type 1 diabetes care and lack of understanding on how to do this. This protocol paper describes a feasibility and pilot study of the ActivPals programme—an intervention to support active lifestyles in youths with type 1 diabetes.

**Methods/design:**

Key intervention components have been identified from preliminary work (individual and family focus, peer mentoring, technology integration and improved communication and understanding) and are being developed into a pragmatic randomised controlled trial (RCT) supported by recruitment pathways. A steering group of health care professionals and managers will refine the intervention to patient needs. A pilot trial is providing data on intervention implementation, acceptability and feasibility. Twenty youths with type 1 diabetes are being recruited and randomised into an intervention or control group. Physical activity is being measured objectively using the Actigraph GT3X+ monitor at baseline and 1-month follow-up. Contextual factors associated with intervention delivery are being explored.

**Discussion:**

This study will contribute to the development of evidence-based, user-informed and pragmatic interventions leading to healthier lifestyles in youths with type 1 diabetes.

## Background

Type 1 diabetes is a chronic disease where the insulin-producing pancreatic beta cells are destroyed resulting in an inability of the body to regulate blood glucose. The condition is managed by regular monitoring of blood glucose, administering insulin and participating in a healthy diet and regular physical activity [1]. Diabetes has been a growing public health burden across the world [2] with treatment for type 1 diabetes costing the NHS in England roughly £1.802 billion a year [3]. The global incidence of type 1 diabetes is rising with an estimated 70 % rise in the disease by 2020, in European adolescents under age 15 [4]. Despite significant improvements in technology for blood glucose management, youths with type 1 diabetes continue to suffer from poorer health, relative to peers without diabetes. For example, research suggests there are higher mortality rates, more cardiovascular risk factors, higher rates of depression, lower educational attainment and poorer psychosocial health outcomes [5, 6].

Glycosylated haemoglobin (HbA1c) is a measure of glycaemic control and is considered by both patients and health care professionals to be at the core of type 1 diabetes management [7]. HbA1c is an important marker for risk of developing micro- or macrovascular complications of diabetes (such as retinopathy, nephropathy, cardiovascular disease and cerebrovascular disease) [8]. Diabetic complications develop as a result of chronic hyperglycaemia which causes damage to tissues and can develop as early as 2 years from diagnosis [9]. Improving HbA1c is therefore a priority for youths with type 1 diabetes.

There is now a small body of evidence which suggests regular physical activity (PA) can significantly reduce HbA1c levels in individuals with type 1 diabetes [7, 10, 11]. This builds on the prolific evidence showing the positive physical and psychological benefits of regular PA in childhood and adolescence [12]. Regular physical activity is therefore recommended in clinical guidelines as one of the core elements of good type 1 diabetes management [13]. Despite appreciation for the benefits of physical activity, evidence suggests youths with type 1 diabetes are less physically active than peers without diabetes [14–16]. For example, a recent study [16] found that young people with type 1 diabetes aged 7–9 and 12–14 years spent on average 78 % (10.2 h/day) of the waking day sedentary and 43 min/day participating in moderate to vigorous PA. Sedentary behaviour is a distinct class of behaviours (i.e. sitting, watching television, playing video games) that is characterised by little physical movement and low energy expenditure [17]. Only two of the 40 participants in the study achieved minimum guidelines of PA participation of 60 min moderate to vigorous intensity PA (MVPA) on each accelerometer wear day, and 19/40 did not achieve 60 min of MVPA on any day. As PA levels are well below the recommendations for health and sedentary behaviour is high in youths with type 1 diabetes, there is clearly a need for intervention studies to support this population to lead an active lifestyle.

Whilst there have been a variety of published intervention studies with youths with type 1 diabetes, there are limitations with this work. For example, interventions have not been based on behavioural change theories [10, 18], have uncontrolled designs [19, 20], or consist of a very structured supervised intervention design (e.g. using supervised structured exercise classes in the intervention) [20–24]. Whilst short-term changes in PA might be evident with such supervised settings, often, the PA behaviour reverts back to pre-intervention levels when the supervised intervention is removed [25]. No study has been conducted, to our knowledge, which is theoretically based, adopts a randomised controlled design and has been tailored to young people and families with type 1 diabetes to support long-term lifestyle behaviour change. As such, there is a need for new, higher quality (evidence informed and theoretically based) interventions, which are developed using the UK Medical Research Council (MRC) framework [26].

The MRC framework for evaluating complex interventions will be used as the basis for this research [26]. The framework strongly advises carrying out feasibility and pilot work prior to running a full-scale trial; therefore, in keeping with phases 1 and 2 of the MRC framework, this study proposes to examine the feasibility of recruitment, retention and acceptability of an RCT PA intervention for youths with type 1 diabetes (see Fig. 1). This study aims to (1) develop a theoretically based tailored lifestyle intervention (ActivPals programme) to support active lifestyles for youths with type 1 diabetes and to (2) explore the feasibility of delivering this intervention. The ActivPals programme is being developed from previous work with youths with type 1 diabetes, which highlighted the importance of peer and parental support when leading an active lifestyle. This work will provide critical information for the development of a definitive trial, in addition to providing important information for improving clinical care of type 1 diabetes in youths. The intervention consists of two key phases:

**Fig. 1 Fig1:**
[figure not shown]
MRC framework for designing and evaluating complex interventions

Phase 1 specific objectives are to develop:An intervention (ActivPals programme) to support active lifestyles in youths with type 1 diabetesFeasible recruitment pathways towards the intervention

Importantly, the intervention and recruitment pathways will be evidence based whilst being pragmatic and suitable for integration within current type 1 diabetes NHS practice.

Phase 2 specific objectives are to recruit participants and conduct a pilot and feasibility trial to determine:The recruitment, initial retention and adherence level that can be achieved for a 4-week intervention programme in both the intervention and control groups.Preliminary evidence of effects of the intervention on physical activity, sedentary behaviour and quality of life. This will provide a preliminary indication of whether the intervention can show change within this group. Following this, an effect size will be estimated for a ‘definitive’ randomised controlled trial.The acceptability of the intervention recruitment pathways and intervention content, delivery, duration and intensity to participants and health professionals.

## Methods

### Study population

Participants will be included in phase 1 of the research if they meet the following inclusion criteria:Aged between 7 and 16 who have a medical diagnosis of type 1 diabetes (a medical professional will have previously tested glycated haemoglobin (HbA1c) levels and provided a diagnosis)Are registered in Greater Glasgow and Clyde Children’s Diabetes ServiceAre independently ambulatory

Parents and carers of possible participants will also be invited to support the individual in participation. Individuals will not be eligible to participate in the study if they have:Been advised not to undertake physical activity by their doctorSevere learning disabilities and not able to understand the study protocolSevere challenging behaviour or other needs requiring constant one to one support

### Recruitment

Researchers have identified the need for a recruitment strategy in RCTs [27, 28]. A strategy has been designed to guide the recruitment process. The full strategy is shown in Appendix. Participants will be recruited to phase 2 via three recruitment points: (1) from paediatric diabetes clinics (main recruitment site), (2) through support groups or clubs for young people with type 1 diabetes and (3) the diabetes nurses working at the hospital will screen the medical records of paediatric patients registered at the clinic for eligibility to participate in the study. To ensure patient confidentiality, clinic staff will screen the patient records and only retrieve information on participant’s age, any exclusion criteria and next appointment date. The staff and researcher will not discuss any information on patient files. The researchers will assess the most effective recruitment routes which will inform future work with this population. There are three type 1 diabetes clinics per week at Yorkhill hospital (the main recruitment site) and others across Greater Glasgow and Clyde paediatric diabetes service. Greater Glasgow and Clyde is the largest urban area in Scotland and the fifth largest in the United Kingdom (UK) [29], therefore offering a fairly representative sample of young people living in urban areas in the UK. Participants who attend a paediatric diabetes clinic and meet the inclusion criteria will be informed of the study by the researcher or by the paediatric consultant, diabetes doctors and nurses. Those who are eligible and interested in participating in the study will be given an information pack which will include more details about participation. Participants can express interest in the study by signing and returning a tear-off slip in the information pack and posting it using the self-addressed envelope provided. The researcher will then contact participants and arrange a visit to discuss the study. A strong collaboration between the research group and the diabetes health care team has already been established based on previous research carried out with this population [10, 16].

### Consent and randomisation

Participants who are interested and eligible to participate will be randomised individually to the intervention or control group. As this is a small-scale feasibility and pilot study, the researcher collecting the data will also deliver the intervention. Therefore, it is not possible for the researcher to be blind from the treatment group. Another member of the research team (the PI) will randomise participants and write the treatment allocation for each participant on a piece of paper. This will be placed in a sealed envelope, only to be opened by the researcher immediately before the intervention/control group visit. Consent/assent will be sought at two stages: firstly, for permission from the carer to be contacted by the researcher to arrange appointments and, secondly, written consent/assent to opt into participate in each aspect of the study (physical activity intervention component and interview component). This will be sought at the study visits, once the researcher has discussed the study in detail with participants. Written information sheets will be given to participants (young people and parents/carers). The researcher will go over the information sheet with participants at the first visit to ensure that participants understand the study protocol and what is being asked of them.

### Withdrawal of study participants

The participants will be given every opportunity to clarify points they do not understand and, if necessary, ask for more information. Participants will be given sufficient time to consider the information sheets provided. It will be emphasised that the participant may withdraw their consent to participate at any time without loss of benefits to which they otherwise would be entitled. Participants will only be withdrawn from the study by the researcher if the researcher perceives them to be at risk or if there is a serious adverse event. If there is a serious adverse event (e.g. injury from exercise, medical help sought for diabetes), the details of this will be recorded on a Serious Adverse Event form, provided by the local NHS board and national good clinical practice will be followed. The researchers will monitor any adverse events during the study.

## ActivPals intervention

The ActivPals intervention aims to:Support youths with type 1 diabetes to initiate and maintain an active lifestyle, including increased MVPA and reduced sedentary behaviourBe endorsed by NHS diabetes care staff highlighting a clear integration of physical activity into diabetes care and be of a duration and intensity realistic for roll out in practice

The theoretical framework for the intervention will draw on Social Cognitive Theory [30], which emphasises the importance of self-efficacy and setting realistic goals. Models of peer support [31], defined as ‘support from a person who has experiential knowledge of a specific behaviour or stressor and similar characteristics as the target populations’, will also be the key to the intervention. The ActivPals intervention will be tailored to the individual’s baseline activity, activity preferences and local opportunities. The inclusion of one or two parents or carers or other support person throughout the full intervention period will be strongly encouraged. The intervention will be delivered by the researcher (first author) who is collecting the data for the study. The intervention consists of (1) an initial physical activity consultation [32] incorporating behaviour change techniques and (2) the use of role modelling/peer mentors (athletes and roles models with type 1 diabetes have endorsed the research and have provided video messages to support young people with type 1 diabetes to be more active). The third key component of the intervention is the use of a wearable self-monitoring device which syncs to a mobile app and website. Continued support using social media/electronic SMS text messages, telephone contact or email will also be made by the researcher to encourage participants to adhere to their physical activity plan. See Fig. 2 for a diagram of the intervention components.

**Fig. 2 Fig2:**
[figure not shown]
ActivPals PA intervention components

### Phase 1 (4 months): aim—development of intervention and recruitment pathways

The researchers have identified the key components of the intervention that will be developed and piloted based on prior work with this population. A steering group of diabetes health care professionals and individuals at management level will be established, using the James Lind Alliance framework. The steering group will advise on how these key components are implemented and will assist with refining the intervention. The steering group will help to guide the intervention to the needs of patients, tailor intervention delivery within current clinical practice and support dissemination to a broader audience of patients and diabetes educators.

### Physical activity consultation

The researchers have carried out previous work to identify important components of an intervention [10, 16]. This includes incorporating behaviour change techniques, education and support for diabetes preparation and a combination of group and one to one support. A physical activity consultation aligns well with these identified components and has been successfully used with other diabetes groups [32]. Guidelines on conducting this consultation have been published for use in adults with diabetes [32]. The consultation will involve an individual or group discussion around physical activity and sedentary behaviour and aims to increase motivation, provide education and develop an individual tailored plan for supporting an active lifestyle. Strategies and techniques identified as important for supporting behaviour change are incorporated to support initiation and maintenance of an active lifestyle. Examples of strategies which may be included are investigating current physical activity behaviour; discussing benefits, barriers and costs of becoming more active; identifying suitable activities; establishing and enhancing social support and self-efficacy; setting personal goals and discussing relapse prevention (Fig. 2).

**Fig. 3 Fig3:**
[figure not shown]
Study flow chart

### Role modelling/peer mentors

Often, group structured education sessions are offered as part of diabetes care. Group/peer support has been identified as an important component of an intervention to support active lifestyles in our previous research [10, 16]. During the development of the ActivPals intervention, we will explore how the intervention could be integrated with current diabetes group education sessions. In particular, group sessions offer an opportunity to incorporate peer support, involving sharing experiences, mentoring and role-modelling. The suitability and feasibility of including peer support within group educations will be explored during intervention development. In addition, the inclusion of role models/peer mentors will be examined. Peer mentors will be athletes with type 1diabetes identified by the researchers. Motivational videos will be provided as part of the intervention, which will contain information about the benefits of physical activity participation, particularly when living with type 1 diabetes. Participants will be given the link to the ‘YouTube’ videos and encouraged to watch these regularly in their own time, over the intervention period, to increase PA.

### Continued support through social media/emails or telephone contact

We will explore the possible use of social media, emailing or telephone support as a mechanism for continued support and to provide further information on aspects of diabetes management.

### Phase 2 (8 months): aim—feasibility trial

Once the ActivPals intervention has been developed, we will conduct a feasibility study to explore intervention feasibility and test practical aspects of study design. Based on previous literature, an effect size will be estimated for a subsequent definitive randomised controlled trial.

### Pilot procedures

Participants (child and parent/carer) will be visited a minimum of four times during this pilot study. During visit 1, basic demographic (gender, age), medical information (body mass index, diabetes duration and current therapy), PA and QoL questionnaires (see primary and secondary outcome measures section) will be completed and participants will be given an Actigraph activity monitor and asked to wear this for the next 7 days. An accelerometer wear diary will be given to participants to record attachment and removal.

Visit 2 will occur approximately 8 days later. At this point, activity monitors and wear diaries will be returned and participants will then be randomised into the intervention or control group. At this point, the researcher will open the envelope to reveal the treatment group. Those who have been allocated to the intervention arm of the study will receive the PA consultation and intervention materials. The intervention period will last 4 weeks, after which visit 3 will take place. During this visit, both intervention and control participants will once again be given an Actigraph activity monitor and asked to wear this for the next 7 days. An accelerometer wear diary will again be given to participants to record attachment and removal. Visit 4 will occur approximately 8 days later during which time activity monitors and wear diaries will be returned. Participants will be asked to complete the PA and QoL questionnaires with the researcher. Intervention participants will be invited to participate in a short interview to explore views on the ActivPals intervention programme. At this point, participants in the control group will be offered the physical activity intervention, followed by an interview. A wait list control design will be used as it would be unethical to deny participants’ access to an intervention which we believe is likely to be beneficial to health. See Fig. 3 for study flow chart. More details on the pilot study design are noted below following the PICOT protocol (e.g. Population, Intervention, Comparison group, Outcome measures (feasibility and patient centred) and Timing).

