Generic and disease-specific questionnaires will be used to measure quality of life in participants. The PedsQoL 4.0 Generic Core Scale was used to measure general quality of life [38]. This 23-item questionnaire contains the following subscales: physical functioning, emotional functioning, social functioning and school functioning. A psychosocial health summary score will be calculated from the average of the emotional, social and school functioning subscales, a physical health summary score (from the physical functioning subscale) and a total overall score from the average of all subscales. This scale has shown good reliability and validity in this population [38, 39]. The PedsQoL 3.0 type 1 Diabetes Module is a 28-item questionnaire measuring diabetes-specific QoL consists of five subscales: diabetes symptoms, treatment barriers, treatment adherence, worry and communication. Patients (self-report) and their parents (proxy-report of the child’s QoL) will complete questionnaires by rating items on how much each was a problem in the previous month using a 5-point Likert scale (‘0’ = never a problem; ‘4’ = almost always a problem). This questionnaire has been validated and has shown to be reliable in children with type 1 diabetes [38, 40]. Changes in general QoL and diabetes module scores will be analysed between intervention and control groups to asses for any trends in intervention effects.

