### Limitations of the research

As this is a small-scale pilot and feasibility study, the researcher (first author) will be recruiting participants, collecting the data and also delivering the intervention. Whilst we acknowledge that a double-blind pilot RCT would strengthen the design of the study, there is limited time and resource with this small-scale pilot study. Therefore, any future funding applications to test the effectiveness of the intervention would include costs for a health professional and research assistant to avoid potential biases in the trial design. Researcher bias will be reduced in the qualitative element of the study as an MSc student, independent to the study, will be conducting the interviews.

The time and funding limitations also restrict the possibility of collecting post-intervention/control follow-up data. Thus, it is not possible to assess long-term effects of the intervention in this small pilot study. These limitations will be addressed in the next phase of work.

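### The visit 4 activity and QoL questionnaires are completed with the unblinded researcher who coached only the intervention arm, an avoidable source of differential response bias in secondary outcomes

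*Protocol article*

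**What the plan says.** Under Pilot procedures, the follow-up forms are handled at visit 4, after the second week of monitor wear: "Participants will be asked to complete the PA and QoL questionnaires with the researcher". Baseline forms are completed at visit 1, before allocation is revealed at visit 2; the article does not say who is involved in completing them.

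Consent and randomisation explains that "the researcher collecting the data will also deliver the intervention", and that "it is not possible for the researcher to be blind from the treatment group". The ActivPals intervention section confirms it: "The intervention will be delivered by the researcher (first author) who is collecting the data for the study". It adds that "telephone contact or email will also be made by the researcher to encourage participants to adhere to their physical activity plan".

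Patient-centred outcome measures describes the QoL instruments as completed by both generations: "Patients (self-report) and their parents" as proxies, who "will complete questionnaires by rating items on how much each was a problem in the previous month using a 5-point Likert scale". The activity questionnaire is a seven-day recall given with a parent's or carer's help. QoL changes are compared between arms, and Statistics and data analysis names an ANOVA for changes in activity and QoL.

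Limitations of the research discloses that one person recruits, delivers and collects data, for reasons of time and resource. The one safeguard it names is for the qualitative part: "an MSc student, independent to the study, will be conducting the interviews".

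**The concern.** Self-rated and proxy-rated answers are open to the wish to please. By visit 4, intervention families have had a consultation, agreed an activity plan and been encouraged to keep to it by the person with whom they now fill in the forms. Control families have met the same person but have not been coached. If this moves answers in one arm more than in the other, the movement appears as an intervention effect on QoL and reported activity, and no analysis of these data can separate the two.

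What is at stake is limited but real. Preliminary evidence on quality of life is one of the phase 2 objectives, and the same objective leads on to an effect size for a definitive trial. Treating the results as pilot data deals with imprecision. It does not deal with a directional bias.

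**Working it through.** The document gives no figure to reproduce: the total of 20 has no alpha, power, SD or target effect behind it. The check is therefore a reading of the text, followed by an illustration on assumed inputs.

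**Step 1. Is it the same person?** Yes. Consent and randomisation, ActivPals intervention and Limitations all say that the deliverer collects the data, and the first of these says that this person is not blind.

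**Step 2. Are the outcomes open to influence?** The QoL ratings and the activity recall are. The primary outcome, MVPA and sedentary time, comes from the Actigraph record of the week between visits 3 and 4. How the questionnaires are completed does not alter it.

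**Step 3. Would change from baseline cancel the bias?** Let b_I and b_C be the shifts in answers at follow-up caused by completing the forms with this researcher. At baseline nobody knows the allocation, so any shift is equal between arms in expectation. Then

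observed difference in change = true effect + (b_I − b_C).

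A shift common to both arms cancels. The difference remains, because the coaching takes place between the two measurements and in one arm only. Controls are offered the programme only after their follow-up measures.

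**Step 4. Is the step separable from the disclosed dual role?** Yes. Handing over and collecting forms is data collection. Being involved while they are filled in is a further choice. The instruments are meant for self and proxy completion, and parents already help with the activity questionnaire.

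**Step 5. Could the pilot detect the bias?** Assumed: 10 per arm (no allocation ratio is given) and SD = 1 for the analysed score. The standard error of the difference is √(2/10) = 0.447 SD. A bias of 0.1 to 0.5 SD could not be told apart from noise or effect.

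**Step 6. What if it were carried into planning?** Assumed: a definitive trial sized on QoL, two-sided alpha 0.05, 80% power, 1:1, SD = 1. Per arm, n = 2(1.96 + 0.842)²/d² ≈ 15.7/d². Real power is Φ(d_true·√(n/2) − 1.96).

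| True effect (SD) | Bias (SD) | Planned n per arm | Real power |
|---|---|---|---|
| 0.3 | 0 | 175 | 80% |
| 0.3 | 0.1 | 99 | 56% |
| 0.3 | 0.2 | 63 | 39% |
| 0.3 | 0.3 | 44 | 29% |
| 0.5 | 0 | 63 | 80% |
| 0.5 | 0.1 | 44 | 65% |
| 0.5 | 0.2 | 33 | 53% |
| 0.5 | 0.3 | 25 | 42% |

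For example, with a true effect of 0.3 and a bias of 0.2, the trial is planned on 0.5: 15.7/0.25 = 62.8, so 63. Real power is Φ(0.3 × √31.5 − 1.96) = Φ(−0.28) ≈ 39%. These rows show sensitivity. They do not estimate the bias in this study.

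**The case against.** The strongest reply is that this is part of a limitation already declared. One person does everything for lack of resource, and a later trial is promised separate staff. That answers a complaint about non-disclosure or about blinding in general. It does not answer this point, because private completion needs no further staff.

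Second, a reader might infer that Pilot procedures contradicts the self- and proxy-report description. It does not. Completing a form with the researcher may mean no more than in that person's presence, with child and parent still giving the ratings, and a condensed article need not say which. Presence alone is still enough for the concern, though a weaker form of it.

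Third, a reader might infer that controls have no relationship with the researcher. They do: the same person recruits them, visits them and follows them through four visits. The difference between arms is one of degree, and its direction, probably in favour of the intervention, is plausible and not demonstrated.

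Fourth, it is tempting to put a courtesy shift of 0.2 to 0.5 SD on the bias, or to call it as large as the effect a definitive trial would seek. The document supports neither figure and states no target QoL effect. Nor is it settled that questionnaire effects would size that trial. Strengths of the research stresses activity and sedentary behaviour, and the phase 2 section takes the effect size from earlier literature, whereas the phase 2 objectives place it after the pilot's own evidence.

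Fifth, the MSc student might look like a free replacement. The document gives the student no role at visit 1 or at the control arm's visit 4, since control interviews come after their later intervention. Using the student only where interviews already take place would make completion differ by arm.

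Finally, QoL is examined only for trends, in a study that calls itself underpowered. That limits the weight of the point but does not remove it.

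**Conclusion.** The point holds for the secondary outcomes. The way the visit 4 questionnaires are completed creates a plausible differential response bias in the QoL and reported-activity comparisons. Its size is unknown and cannot be derived from the document. The conclusion rests on two things: the text, which puts the unblinded deliverer at the completion of the forms, and the assumption that four weeks of one-arm encouragement changes how families answer that person. It does not reach the accelerometer outcome, and it does not make the self-report description false. With allocation known to families, some response bias would remain under any mode of completion. This is a cheap improvement worth making, and not a flaw that undermines the pilot.

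**What to change.** Change the visit descriptions in Pilot procedures so that, at visits 1 and 4 and identically in both arms:

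- child and parent each complete their forms privately, before any discussion with the researcher;
- the forms go into a sealed envelope marked with the study number only;
- where a young child needs reading help, the parent gives it after completing and sealing the proxy form, and the help is recorded. The parental help already planned for the activity questionnaire can follow the same order.

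The MSc student is not required, and no staff are added. The costs are a few more missing items and less independence between child and proxy reports for the youngest. Both can be counted as feasibility data, which suits the article's intention to consider missing data and the acceptability of the measures when designing the full trial.

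The article reports that recruitment ended in March 2016 with the study still under way, so the change may come too late for some or all visits. In that case, report how the forms were completed at each visit, do not use questionnaire effects to plan the definitive trial, and adopt private completion there.
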